## Discussion

The current study: (1) evaluates levels of stress, mental health, and stress biomarker salivary cortisol for currently and recently abused women and non-abused controls, across three time periods over 6 months; (2) explores whether there are altered diurnal patterns of cortisol secretion within this sample; and (3) identifies socio-demographic, abuse and mental health predictors of diurnal cortisol parameters. The study protocol and participant documentation have been amended based on guidance from our research advisory group (five former SURVIVE users) and the pilot study. This study is methodologically strong compared to very few neuroendocrinological studies previously conducted in abused women. Firstly we use three-point saliva sampling protocol across three time periods over 6 months which enables us to obtain the key diurnal cortisol parameters prospectively – the diurnal cortisol slope, the size of awakening response, and the average cortisol exposure across the day. Secondly we shall collect data on a number covariates related to diurnal cortisol secretion in order to control neuroendocrine variables for potential confounding. Thirdly UPLC-MSMS will be used to measure salivary cortisol. UPLC-MSMS is a superior technique to traditional immunoassay steroid methods, with improved sensitivity and specificity which is able to measure both salivary cortisol and cortisone (cortisol metabolite) in the samples simultaneously. Fourthly to measure stress, mental health and abuse we use international validated questionnaires. Finally our targeted sample size is larger than those reported in earlier studies in women exposed to DVA which allows performance of subgroup analysis stratified by mental health status, and characteristics of DVA.

This study should add significantly to our understanding of the physiological mechanisms of DVA and explain causal pathway between abuse and mental health consequences in female survivors. It will improve understanding of neuroendocrine markers associated with abuse and mental health status, potentially leading to studies of prognosis and more targeted management of women who have experienced DVA and its sequelae. Ultimately it might be possible to better target intervention for women experiencing DVA with and without specific mental health sequelae in relation to activity of HPA axis. The current study represents a step on this direction.

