It is evident that most investigators have reported different patterns of alterations in diurnal cortisol output in women exposed to childhood abuse (CHA) and DVA. However there are researchers who have concluded that cortisol is a marker of abuse exposure rather than mental health diagnosis [27,28]; others stated that alteration in cortisol output is a correlate of abuse-related mental disorder [29,30]. Currently, it is known that CHA influences the psychobiology of cortisol function and that there is a development from hyper secretion of cortisol to hypo secretion by early adulthood [14]. It is also known that both physical and psychological DVA have significant impacts on the neuroendocrine system of women [27]. At the same time it is not clear whether currently and recently abused women, who have abnormal diurnal cortisol profiles, demonstrate poorer mental health outcomes and how this may correlate with type, severity, duration and cessation of abuse. There is a hypothesis that DVA survivors may be characterized by alterations in HPA axis activity [31] and that further longitudinal studies are needed to identify specific stress system disturbances in this group [2,32]. The current research study aims to investigate the role of the HPA axis on the impact of DVA on women’s mental health. This study tests the hypothesis that compared to non-abused controls all abused women have altered diurnal rhythm in cortisol secretion and that the pattern of this alteration is predicted by abuse characteristics, such as its type, severity, duration, and cessation.

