### Study objectives

1. To evaluate the key diurnal cortisol parameters (diurnal cortisol variation, CAR, and mean cortisol concentration) in women with a current or recent experience of DVA

2. To estimate whether cortisol parameters are associated with type, severity, duration and cessation of abuse

3. To investigate whether cortisol outcomes act as a mediator between the features of abuse and mental health state

4. To examine whether there is any distinction in cortisol levels between those women exposed to both CHA and DVA and those experienced only the latter

5. To explore whether cortisol secretion differs between women, living in a domestic violence refuge and those still living in the community (after adjustment for confounding effects of abuse severity and continuing contact with abuser).

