Upon completion of questionnaire and anthropometry study participants will be given a saliva sample collection kit that includes a saliva collection device (Salivette tubes) with cotton pledget, an illustrated instruction sheet written in plain language explaining the procedure and providing helpful hints (such as putting the tube next to the bed for morning sample), a saliva collection diary in which participants can record experiences on the day of sample collection and a prepaid packaging addressed to the accredited laboratory compliant with current postal regulations. The participants will be asked to collect three saliva samples as soon as possible after questionnaire survey:

1. Sample 1 “bedtime” – right before getting into bed.

2. Sample 2 “awakening” – next morning as soon as the woman wakes up and is ready to get up for the day.

3. Sample 3 “post-awakening” – 30 minutes after taking awakening sample.

Saliva will be collected by either passive drooling into the tube or by chewing (for 2 minutes) the cotton pledget provided with each tube. Participants must have waited at least 30 minutes after smoking, consuming any food or drink or teeth brushing before collecting the saliva sample. Tubes will be labeled with patient identifier and returned to the laboratory by post or via collection by the researcher. Upon arrival to the laboratory tubes with saliva will be centrifuged to remove the upper saliva layer for subsequent measurement of cortisol. The primary tube including the cotton pledget with individual cells will be then discarded in routine clinical waste. The upper saliva layer will be frozen until analysis. The saliva samples will be analyzed in the Department of Clinical Biochemistry at the Bristol Royal Infirmary using Ultra performance liquid chromatography – tandem mass spectrometry (UPLC-MSMS). The analysis also simultaneously measures cortisone a metabolite of cortisol as an additional measure of circulating cortisol [41,42].

To collect data on known covariates that have been related to diurnal cortisol secretion participants will complete saliva collection diary [22]. Data collected on the day of saliva sampling include: schedule (whether weekend vs. weekday), time of awakening, lifestyle (smoking, alcohol use, caffeine, exercise/activity level, perceived stress and negative mood, recent meal, medications) and menstrual timing.

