### Statistical analysis

For the sample size calculation we used findings from similar studies in comparable populations [24,43,44]. Thus, the number of participants required to detect a standardized difference in cortisol levels of 0.5 between abused women and non-abused controls with 80% power using a cut-off score for statistical significance of 0.05 is 128 (64 per group). Assuming 40% drop out rate before the study ends, around 213 eligible subjects would have to be approached. Assuming 60% response rate we will have to approach approximately 355 women, so 213 would consent to join the study, and of these 128 would be expected to complete the study.

Data will be coded and entered into research database during data collection by the two researchers responsible for recruitment. Stata software will be used for statistical analysis. All data will be checked for expected ranges, presence of outliers and abnormal values.

Sample will be analyzed by comparison of participant exposed to DVA and participants without DVA exposure on the basis of cortisol and mental health state data. Primary study outcome will be reported as diurnal cortisol variation, the degree of decline in cortisol across the day. Secondary study outcomes include CAR, size of post-awakening surge in cortisol that occurs in 30 minutes after awakening and mean salivary cortisol concentration across the day. As an additional measure of tissue cortisol the three saliva samples, awakening, post awakening, and bedtime, will also be assayed for cortisone.

Following descriptive statistics for all the cortisol and mental health outcomes, relationship between them will be investigated using appropriate linear (and, for binary outcomes, logistic) regression models. Using the CAS and CTQ data, these techniques will also be used to investigate the extent to which cortisol measures act as potential mediator between the type, duration and cessation of abuse and mental health condition for this group of women.

Missing data from women who dropped out of the study will be handled first by comparing their baseline variables with those who completed the study, and secondly using imputation techniques [45].

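### Same-day perceived stress and negative mood are listed among the covariates to be controlled as confounders, although on the protocol's own model they plausibly lie on the path from abuse to cortisol

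*Protocol article*

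**What the plan says.** All references are to the protocol article.

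- **Measurements.** Participants keep a saliva diary whose stated purpose is to record known covariates of diurnal cortisol. Its entries include weekday or weekend, waking time, menstrual timing and a lifestyle group containing "exercise/activity level, perceived stress and negative mood, recent meal, medications".
- **Discussion.** As a strength of the study, the investigators will "collect data on a number covariates related to diurnal cortisol secretion in order to control neuroendocrine variables for potential confounding". Stress and mood are not set apart from the other diary items.
- **Background.** DVA is described as a form of stress, with the HPA axis as a candidate mechanism. The hypothesis is that abused women differ from non-abused controls in diurnal cortisol rhythm.
- **Statistical analysis.** The sample is sized to "detect a standardized difference in cortisol levels of 0.5 between abused women and non-abused controls". Power is set at 80% and the significance level at 0.05. The main comparison is DVA-exposed against unexposed women, and no covariates are named for it.
- **Childhood abuse (CHA).** The Background says "it is known that CHA influences the psychobiology of cortisol function". The CTQ is collected. Objective 4 uses it among DVA-exposed women: "To examine whether there is any distinction in cortisol levels between those women exposed to both CHA and DVA". The comparison group there is women exposed to DVA alone. The Statistical analysis section also uses CTQ data in the mediation regressions.

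**The concern.** A variable related to cortisol is not a confounder for that reason alone. To be adjusted for in a total-effect analysis, it should not be a consequence of the exposure. On the protocol's account, abuse is a stressor, so higher stress and lower mood on the sampling day may be part of how abuse alters cortisol.

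Mood raises a second problem. Objective 3 treats cortisol as a possible mediator between abuse and mental health. On that model negative mood may also be a consequence of cortisol, and adjusting cortisol for it would condition on something downstream of the outcome.

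What is at stake is the meaning of the primary result. The hypothesis concerns whether abused women's cortisol differs from that of controls. With stress and mood in the model, the coefficient answers whether it differs among women with equal stress and mood. A null answer to the second question could be misread as a null answer to the first. A larger sample would not cure this.

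**Working it through.** **1. The plan's own figure.** Inputs from Statistical analysis: d = 0.5, power 80%, significance level 0.05, equal groups. Sidedness is not stated. A two-sided two-sample t-test needs 63.8 per group, so 64 per group and 128 in all, with power 0.801. The one-sided normal approximation gives 50 per group, so the calculation is evidently two-sided. The recruitment figures also reproduce: 128/0.6 = 213.3 and 213/0.6 = 355. No stated figure is wrong.

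**2. What adjustment does to the target.** Let *p* be the share of the 0.5 SD total effect that runs through diary stress and mood. The adjusted contrast is then d_adj = 0.5 × (1 − p). The documents give no value for *p*, so the following is illustrative. It uses 64 per group, two-sided 0.05 and an unchanged standard error.

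| Assumed p | d_adj | Power |
|---|---|---|
| 0 | 0.500 | 0.801 |
| 0.25 | 0.5 × 0.75 = 0.375 | 0.558 |
| 0.50 | 0.5 × 0.50 = 0.250 | 0.289 |

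**3. Allowing for the change in standard error.** Let dM be the group difference in stress/mood in SD units, assumed to be 0.5 to 0.8. With equal groups the variance inflation is 1 + dM²/4, that is 1.0625 to 1.16. The mediator slope is b = 0.5p/dM and the residual variance is 1 − b². The effective size is d_adj / √[(1 − b²)(1 + dM²/4)].

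| Assumed p | d_adj | Power, dM = 0.5 | Power, dM = 0.8 |
|---|---|---|---|
| 0 | 0.50 | 0.78 | 0.74 |
| 0.2 | 0.40 | 0.60 | 0.56 |
| 0.4 | 0.30 | 0.43 | 0.37 |
| 0.6 | 0.20 | 0.28 | 0.20 |

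The conclusion of step 2 does not depend on holding the standard error fixed.

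**4. Direction.** Steps 2 and 3 assume that the direct and mediated parts share a sign. The Background reports lower cortisol in abuse-related PTSD, but higher cortisol with anxiety, depression and the stress of separation. If the mediated part opposed the total, say −0.125 within a total of 0.5, the adjusted contrast would be 0.5 + 0.125 = 0.625, larger than the total effect. The distortion can therefore go either way.

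**5. Childhood abuse (secondary).** The bias from leaving out a binary confounder is its effect on the outcome times its difference in prevalence between groups. The documents give neither. Assuming an effect of 0.3 to 0.5 SD in either direction and a difference of 10 to 40 percentage points, the bias ranges from 0.3 × 0.10 = 0.03 SD to 0.5 × 0.40 = 0.20 SD. That is 6% to 40% of the 0.5 SD target. If there were no DVA effect, the rejection rate would be about 0.05 to 0.20 instead of 0.05.

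**The case against.** The strongest reply is that no model is written down. The Discussion speaks only of a number of covariates, the Measurements section only lists diary entries, and the Statistical analysis section names no adjustment set. The one explicit set belongs to objective 5. Entry of stress and mood into the primary model is therefore implied by joining two sections and is not specified. That is correct and limits how firmly the point can be put. It does not remove it: the diary's purpose and the use of its covariates are both stated, and the text exempts neither item.

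A second reply is that a same-day item mostly captures acute variation, while chronic stress is measured separately by the past-month Perceived Stress Scale, which is not a diary item. The Background also cites a study in which chronic and not acute stress explained raised evening cortisol. This stands in part. A same-day rating mixes day-specific noise with the lasting effect of abuse, which argues for a labelled sensitivity analysis but not for a place in the primary model.

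A third reply is that BMI, smoking and medication may also be affected by abuse, so a rule against post-exposure variables reaches further than these two items. That is fair. The point here is confined to stress and mood because the protocol's own causal account singles them out.

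On childhood abuse, a reader might infer that the plan leaves a known confounder out of the main contrast. The text does not support that. The CTQ is unmentioned there, not excluded, and a condensed article may leave a covariate list to the full protocol. The Discussion also aims to identify abuse-related predictors of cortisol, which could include the CTQ. Nor does any section say that childhood abuse is commoner in DVA-exposed women than in these controls, some of whom will be their friends or relatives. Objective 4 is legitimate as written.

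**Conclusion.** The concern holds for same-day stress and mood. Taken as written, the protocol places two plausible consequences of abuse among the variables to be controlled as confounders, which conflicts with its own causal account and its total-effect hypothesis. If 25–50% of a 0.5 SD effect were mediated with the same sign, power at 64 per group would fall from 80% to about 56–29%. Both the share and the sign are assumptions. A reader might infer that the bias must be towards zero; the opposing cortisol directions cited in the Background do not allow that.

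Childhood abuse is a secondary point only. It is a plausible confounder whose role in the main contrast deserves a sentence. The possible bias of 0.03 to 0.20 SD rests wholly on assumed inputs.

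**What to change.** 1. State that the primary DVA versus no-DVA cortisol contrast is reported without diary perceived stress and negative mood. Keep sampling-day covariates such as waking time and weekday or weekend.
2. Use diary stress and mood only in a sensitivity analysis labelled as such, or in the mediation analysis, and describe the resulting estimate as a partial effect.
3. Also report the main contrast adjusted for CTQ score, described as a plausible confounder. Objective 4 needs no change.

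Every variable is already collected, so the cost is analysis wording. The CTQ-adjusted report takes one degree of freedom and slightly more analysis work.

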## Abbreviations

BMI: Body mass index; CAR: Cortisol awakening response; CAS: Composite abuse scale; CTQ: Childhood trauma questionnaire; DD: Dissociative disorder; DSM – IV: Diagnostic and statistical manual of mental disorders fourth edition; DVA: Domestic violence and abuse; GAD: Generalized anxiety disorder; HPA: Hypothalamic-pituitary-adrenocortical; IPV: Intimate partner violence; MAPSAIS: Miller abuse physical symptom and injury scale; MDD: Major depressive disorder; PHQ: Patient health questionnaire; PSS: Perceived stress scale; PSS-SR: Posttraumatic stress disorder symptom scale - self-reported; PTSD: Posttraumatic stress disorder; SDS: Sheehan disability scale; UPLC-MSMS: Ultra performance liquid chromatography – tandem mass spectrometry.
